Early intervention, as defined in this study, is facilitated by knowledge, attitudes and behaviors that facilitate timely, effective and appropriate support for workers with emerging signs and symptoms of mental health problems or disorders [17]. Support may involve a range of options, from counseling and/or medication from a healthcare provider to connection with an Employee Assistance program or a self-help group. The conceptual model of early intervention guiding the project is outlined in Figure 1. Earlier intervention can be accomplished by augmenting two key health access behaviors; a) workers seeking help when they are struggling with their own mental health issues, and b) workers facilitating appropriate outreach to colleagues who are struggling in order to facilitate their help seeking behavior. Appropriate help seeking and outreach behaviors are considered together because they are the two primary mechanisms by which a worker receives the help that he/she needs, and they share common pathways [6]. Further, actions taken to facilitate early identification and intervention are mediated through reduction of stigma, improved mental health literacy and better attitudes towards professional treatment. This can have a dual effect on both help seeking and appropriate outreach to colleagues. Although the primary outcome of interest in this study is help seeking and outreach behavior, it should be noted that early intervention leads to more appropriate utilization of mental health services and faster recovery from mental health issues. The overall impact of greater efficiency, reduced absenteeism and sick leave, and increased productivity at work should provide economic advantages to both the worker and the employer [13]. Evaluation of these long-term outcomes is beyond the scope of this project, but will be the focus of subsequent research.

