### Data analysis

In accordance with Research Question 1, we hypothesize that help-seeking behavior will increase from baseline to 3 and 6 months by a greater amount in the Beyond Silence group than in the MHFA control. The primary approach to this question is the repeated measures analysis of a checklist of desirable help seeking/help providing behaviors, obtained from the survey at each time point. Overall tests of the change across all three measurements are available from generalized linear mixed-effects analysis, assuming that the count (from 0 to 20 behaviors) is distributed as a Poisson variable. This is a standard approach that accounts for over-dispersion in the Poisson model arising from the repeated measurements, permits the inclusion of participants who have not completed all three assessments, and allows for flexible modeling of the change over time and the inclusion of any relevant covariates [41]. In the primary analysis, the statistical significance of treatment group in this model will be used to address the first research question. In view of the randomized design, the primary analysis will not include additional covariates, but the model will be used to explore modifying effects by including additional covariates (e.g. age, sex, prior experience with mental illness) and interactions between these covariates and treatment group. As a secondary outcome, we will analyze a scaled measure of behavioral intentions using similar linear mixed-effects analysis.

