In Research Question 2, we propose mediating forces that are expected to be different in the two programs, including scaled measures of mental health literacy (expected to be higher in the MHFA group), stigma regarding mental illness (expected to be greater in the Beyond Silence group), and attitudes towards seeking professional help (expected to be higher in the Beyond Silence group). Following recommendations by Baron and Kenny [42], we will initially explore whether changes in literacy occur in association with the interventions. These analyses will use linear regression, modeling change in literacy and stigma, respectively, occurring in association with the interventions. Next, we will use Poisson or negative binomial regression to determine whether changes in literacy, stigma and attitudes associated with intervention (as well as overall levels of each) predict counts on the desirable behavior checklist. If associations are observed in both cases, we will evaluate change in these measures using linear mixed effects as described for Research Question 1. Substantial diminishment, or disappearance, of the effect of the interventions on help-seeking when the potential mediators are included in the model will be interpreted as providing evidence of mediation.

The random assignment of participants to intervention groups eliminates biases in the evaluation of the treatment effects, but the generalizability of this effect in relation to the representativeness of the sample will be assessed by comparing demographic and employment data from study participants to the equivalent data available for the entire organization. This data also provides insight on the reach of the program within the organization in terms of the characteristics of who volunteers to participate in this kind of program. This augments the qualitative analysis of Research Question 3.

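### The mediation rule counts only a shrinking program effect, so it cannot identify literacy, which the plan expects to favour MHFA; the stigma direction and step one also need correcting

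*Protocol article*

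**What the plan says.** The Research questions section asks what mediates the impact of the contact-based program. It then asks separately for the effect of literacy, of attitudes towards coworkers (stigma) and of attitudes towards professional treatment.

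The Data analysis section gives the method and the expected directions:

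- **Total effect.** Behavior is expected to increase "by a greater amount in the Beyond Silence group than in the MHFA control".
- **Literacy.** "scaled measures of mental health literacy (expected to be higher in the MHFA group").
- **Stigma.** "stigma regarding mental illness (expected to be greater in the Beyond Silence group").
- **Attitudes to professional help.** Expected to be higher with Beyond Silence.
- **Step one.** "Following recommendations by Baron and Kenny [42], we will initially explore whether changes in literacy occur in association with the interventions". Then: "These analyses will use linear regression, modeling change in literacy and stigma, respectively, occurring in association with the interventions".
- **Step two.** Poisson or negative binomial regression of the behavior count on literacy, stigma and attitudes. The analysis proceeds if associations appear at both steps.
- **Final rule.** "Substantial diminishment, or disappearance, of the effect of the interventions on help-seeking when the potential mediators are included" in the model is what will be read as evidence of mediation.

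The Background (Importance of early intervention for mental health issues) says that actions towards early intervention "are mediated through reduction of stigma, improved mental health literacy and better attitudes towards professional treatment".

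**The concern.** A rule that looks for shrinkage works when every mediator pushes in the same direction as the total effect. Here the plan itself expects one that does not. If MHFA raises literacy more, and literacy promotes the behavior, literacy narrows the Beyond Silence advantage. Holding it constant makes that advantage larger, and the plan does not say how an increase is to be read.

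Two defects of statement go with this. The stigma expectation points the wrong way for a program built to reduce stigma. The step-one models name two of the three mediators, so the condition that both steps show an association is not defined within the mediation plan for attitudes.

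The literacy-versus-contact contrast is the rationale of the trial, and Research Question 2 names literacy. The final rule cannot answer for it.

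**Working it through.** The plan states no figure for mediation, so there is none to reproduce. The check takes signs from the document and assumes sizes.

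**Signs.** Let *a* be the effect of Beyond Silence versus MHFA on the mediator, and *b* the effect of the mediator on behavior. The total effect *c* is positive (Data analysis).

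| Mediator | *a* (Data analysis) | *b* (Background) | *a·b* |
|---|---|---|---|
| Literacy | − | + | − |
| Stigma, as written | + | − | − |
| Stigma, if lower in Beyond Silence | − | − | + |
| Attitudes | + | + | + |

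**Formula.** In a linear model the adjusted effect is *c′ = c − Σ(a·b)*. It shrinks only if the net indirect effect has the sign of *c*. For a count with a log link this is an approximation.

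**Literacy alone.** Take *c* = 0.44 behaviors, the difference quoted in the Participants section, used here only as a scale. Over a range of assumed |*a·b*|:

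- 0.05: *c′* = 0.44 + 0.05 = 0.49 (+11%)
- 0.10: *c′* = 0.54 (+23%)
- 0.20: *c′* = 0.64 (+45%)
- 0.30: *c′* = 0.74 (+68%)

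The size changes; the direction does not.

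**Joint entry, stigma lower in Beyond Silence.** Let stigma and attitudes each carry an assumed +0.20. Without literacy, *c′* = 0.44 − 0.40 = 0.04, a fall of 91%. With a literacy path of −0.20, *c′* = 0.44 − 0.20 = 0.24, a fall of 45%. With −0.30, *c′* = 0.34, a fall of 23%. The rule still sees shrinkage, but literacy is hidden and the other two are understated.

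**Joint entry, stigma as written.** *c′* = 0.44 − (−0.20 − 0.20 + 0.20) = 0.64, a rise of 45%.

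**Simulation on the count scale.** 1,500 trials per scenario, 100 per group, one Poisson outcome per person with mean 1.5 (middle of the 1–2 in the Participants section), and total log rate ratio ln(1.94/1.5) = 0.257. Assumed: |*a*| = 0.5 SD, |*b*| = 0.3 per SD, and a fall of at least 20% as the meaning of substantial. Clustering by training group was not modelled.

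| Mediators in model | Mean group log rate ratio, stigma as written | Same, stigma lower in Beyond Silence |
|---|---|---|
| None | 0.253 | 0.252 |
| Literacy | 0.404 | 0.400 |
| Attitudes | 0.106 | 0.104 |
| Literacy and attitudes | 0.256 | 0.253 |
| All three | 0.405 | 0.104 |

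Adjusting for literacy lowered the group effect in 0.1% of trials and met the 20% threshold in none, although both literacy paths were significant in 94%. With all three mediators the threshold was met in 0.3% of trials with stigma as written, and in 89% with stigma lower in Beyond Silence.

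**Stigma wording.** The Background lists reduction of stigma as a mediator of early intervention. The section on approaches to workplace support recommends contact-based education to address stigma. The Interventions section gives reducing it as an aim of the Beyond Silence sessions. An expectation of greater stigma in that group contradicts all three.

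**Step one.** The linear models cover literacy and stigma. Step two adds attitudes, and the condition on both steps is then applied to all three.

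**The case against.** The main question asks what explains a Beyond Silence advantage. A variable that is higher under MHFA cannot explain it, so for that question a shrinkage criterion points the right way. Steps one and two would still show that MHFA raised literacy and that literacy predicted behavior. The article does not say that an increase means no mediation, nor whether mediators enter singly or together. It also warns that these relationships are not always predictable, so a material literacy path is possible rather than established.

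Much of this stands, and it limits the point. It does not remove it: the Research questions section asks for the effect of each mediator, and the final rule has no reading for one that works in the opposite direction.

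On attitudes, the Data analysis section plans a secondary mixed-effects analysis of behavioral intentions. If that uses the scale for attitudes to seeking help, the program effect on attitudes is estimated elsewhere. The mediation steps do not say so.

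Two stronger readings are tempting and not supported:

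- **That the rule would report no mediation overall.** Full cancellation needs literacy and attitudes to be equal and opposite with stigma left out. With stigma lower in Beyond Silence, the likely intention, joint adjustment usually shrinks the effect and the rule fires.
- **That using behavior at the final survey would put the mediator first in time.** The outreach item in the Data collection section covers contact over the past 6 months, so the final survey looks back over the period in which the mediators change.

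**Conclusion.** The point holds in a limited form. On the plan's own directions, the shrinkage rule cannot identify literacy as a mediator, and joint entry hides it while understating the mediators that favour Beyond Silence. The direction rests on three stated expectations: Beyond Silence better on behavior, literacy higher under MHFA, and literacy promoting the behavior. The size (+11% to +68% over the assumed range) rests on path sizes that the document does not give. The literacy result is the same on either reading of stigma.

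The stigma expectation contradicts the article's rationale and is probably a slip for a greater reduction. The omission of attitudes from the step-one models is a gap in the stated procedure. None of this touches the primary analysis. It is worth correcting because it concerns a named research question.

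**What to change.** - Replace the shrinkage criterion with a signed indirect effect and 95% confidence interval for each of literacy, stigma and attitudes, reported singly and jointly. Recognise mediation in either direction.
- State the scale of the indirect effect for the count outcome, for example log rate or expected number of behaviors.
- Add attitudes to professional help to step one.
- Correct the stigma expectation to a greater reduction in stigma in Beyond Silence.
- Let the intervals allow for the 16 training groups (eight programs and eight courses, Interventions section), and note that a bootstrap over so few groups is approximate.
- Make no claim that the choice of survey secures temporal order, given the look-back of the outreach item.

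Cost: revised wording and a little more programming. No new data.

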## Discussion

Overall, study findings will be used to analyze the relative value of the Beyond Silence program in promoting early intervention for healthcare workers who are struggling with mental health issues. Future research will explore larger scale implementation in other workplaces, and the longitudinal impact on organizational indicators of productivity.

It is hypothesized that healthcare workers have higher levels of mental health literacy than the general public, therefore contact-based education will be more effective than literacy training in addressing the complex forces that prevent individuals from seeking help for their own mental health problems, or provide help to others who are struggling. Most current studies track knowledge and attitude change, therefore the focus of this study on behavior change (help-seeking and help-outreach) and the forces that contribute to behavior change will add depth to our current understanding of the impact of employee educational intervention.
